#### **v. Treatment planning**

Use of 3D conformal technique is required and beam's eye views may be useful in the design of individual shielding. Dose volume histograms (DVH) for the PTV, normal lung, oesophagus, spinal cord and heart will be calculated in order to obtain full knowledge of the 3D dose distribution.

#### **vi. Dose specification and fractionation:**

The dose will be specified at the ICRU reference point and fully corrected for heterogeneity. The dose distribution within the PTV should ideally be within  $\pm 5\%$  of the prescribed dose, and no more than  $\pm 7\%$  of the prescribed dose.

#### **vii. Definition of the organs at risk**

The spinal cord, lungs, oesophagus and heart will be contoured for dose-volume histograms.

- Both the right and left lungs should be contoured as one structure. Contouring should be carried out using pulmonary windows. All inflated lung should be contoured.
- The spinal cord will be contoured based on the bony limits of the spinal canal. The spinal cord should be contoured starting at least 10 cm above the superior extent of the PTV and continuing on every CT slice to at least 10 cm below the inferior extent of the PTV.
- The oesophagus will be contoured using mediastinal windowing on CTscan to correspond to the mucosal, submucosa, and all muscular layers out to the fatty adventitia. The oesophagus should be fully contoured (from cricoid cartilage to the gastro-oesophageal junction)
- The heart will be contoured along with the pericardial sac. The superior aspect (or base) for purposes of contouring will begin at the level of the superior aspect of the left atrium and extend inferiorly to the apex of the heart.

#### **viii. Beams**

Isocentric treatment technique.

The number of beams will vary according to the position and the volume of the PTV in the thorax and to the maximum dose tolerated by the organs at risk.

The treatment plan will be checked by a qualified radiation oncologist after discussion with the planning team. The dose-volume histogram will help to guide that choice.

#### **ix. Set-up verification**

Cone beam or orthogonal images will be obtained on days 1 to 3 (or 2 to 4) and weekly thereafter.

### **4.3 TWICE DAILY THORACIC RADIOTHERAPY**

#### **4.3.1 Schedule**

- **45 Gy in 30 twice daily fractions** over a period of **19 days** (radiotherapy to start on a Monday), 5 consecutive days a week
- The optimal overall treatment time should be 19 days, up to 21 days is a protocol deviation and should be recorded, above 21 days is a protocol violation.
- The interfraction interval will be 6 to 8 hours.
- using conformal radiotherapy and 4 to 10 MV photons emitted from linear accelerators.

- Thoracic radiotherapy will start on cycle 1 day 22, if possible concurrently with the second cycle of chemotherapy (within 24 hours of day 1, cycle 2 of PE).
- Concurrent chemotherapy will be administered during the intervals between the 2 daily radiotherapy fractions.

#### 4.3.2 Normal tissue constraints

To reduce late damages to the normal tissues the following rules will be applied

- Dose: **1.5 Gy** per fraction
- Maximum spinal cord dose will not exceed **42 Gy**. The spinal cord position must be identified throughout the PTV
- The percentage of lung minus PTV receiving more than 20 Gy will not exceed **35%** (V20=35%, based on dose-volume histograms). The mean lung dose will be recorded
- The heart can receive the total dose (TD) to < 30% of its volume. For > 50% of cardiac volume, dose < 50% of TD is recommended

#### 4.3.3 Treatment Delays

Every effort should be made to deliver the prescribed dose of radiotherapy in 19 days.

If unavoidable delays occur, that could increase the overall treatment time beyond 19 days, e.g. due to machine breakdown, compensation should if possible be made by one of the following mechanisms:

- treating on a weekend day, **or**
- adjusting fraction size to deliver the total prescribed dose within 19 days;  
However, fraction size should remain < 2.25 Gy

If the radiation schedule is interrupted for more than 1 week due to intercurrent illness consideration should be given to discontinuing treatment. Further treatment will depend upon the clinical situation and is at the discretion of the responsible clinician. Interruptions for < 1 week due to intercurrent illness or radiation toxicity will be recorded and treatment should be completed as planned.

### 4.4 HIGH DOSE ONCE DAILY THORACIC RADIOTHERAPY

#### 4.4.1 Schedule

- **66 Gy in 33 daily fractions** over a period of **45 days** (radiotherapy to start on a Monday), 5 consecutive days a week
- The optimal overall treatment time should be 45 days. Up to 47 days is a protocol deviation and should be recorded, above 47 days is a protocol violation.
- using conformal radiotherapy and 4 to 10 MV photons emitted from linear accelerators.

- Thoracic radiotherapy will start on cycle 1 day 22, if possible concurrently with the second cycle of chemotherapy (within 24 hours of day 1, cycle 2 of PE).

#### 4.4.2 Normal tissue constraints

To reduce late damages to the normal tissues the following rules will be applied

- Dose: **2 Gy** per fraction
- Maximum spinal cord dose will not exceed **48 Gy**. The spinal cord position must be identified throughout the PTV
- The percentage of lung minus PTV receiving more than 20 Gy will not exceed **35%** (V20=35%, based on dose-volume histograms). The mean lung dose will be recorded.
- The heart can receive the total dose (TD) to < 30% of its volume. For > 50% of cardiac volume, dose < 50% of TD is recommended

#### 4.4.3 Treatment Delays

Every effort should be made to deliver the prescribed dose of radiotherapy in 45 days.

If unavoidable delays occur, that could increase the overall treatment time beyond 45 days, e.g. due to machine breakdown, compensation should if possible be made by one of the following mechanisms:

- giving two fractions on a subsequent day, with a minimum interval of six hours between fractions, **or**
- treating on a weekend day, **or**
- adjusting fraction size to deliver the total prescribed dose within 45 days;

However, fraction size should remain < 3 Gy.

If the radiation schedule is interrupted for more than 1 week due to intercurrent illness consideration should be given to discontinuing treatment. Further treatment will depend upon the clinical situation and is at the discretion of the responsible clinician. Interruptions for < 1 week due to intercurrent illness or radiation toxicity will be recorded and treatment should be completed as planned.

### 4.5 PROPHYLACTIC CRANIAL IRRADIATION

No later than 6 weeks after the last cycle of chemotherapy, patients without evidence of progressive disease on CXR or CT scan and with no clinical evidence of brain metastases will be given PCI.

Simulation is mandatory for whole brain irradiation. Patients should be treated in supine position. Immobilisation by individual masks or other means is recommended. Treatment will be delivered with megavoltage machines of energies ranging from 4-10 MV photons. Treatment with a single beam is not acceptable. Doses are specified at the mid-plane of two opposed lateral whole brain fields, prescribed to the isocenter. The dose and fractionation of PCI will be left to the discretion of each principal investigator to allow for variation in local practice.

### 4.6 CONCOMITANT MEDICATION

- Prophylactic antibiotics with fluoroquinolones (choice left to local investigator) are recommended to start on day 8 of cycle 1 chemotherapy and to continue for 7 days to minimise the risk of

neutropenic sepsis and respiratory infection. Consideration should be given to continuing prophylactic antibiotics after subsequent cycles if bronchial obstruction is present.

- Anti-emetics will be routinely used using a combination of a steroid and a 5-HT3 antagonist.
- The use of GCSF is optional
  - GCSF will be prescribed, if clinically indicated, as per ASCO 2006 guidelines or in line with local policy / guidelines for treatment of febrile or prolonged neutropenia.
  - Secondary prophylaxis with GCSF is recommended
    - weight < 70 kg: 300 µg days 5 to 12
    - weight > 70 kg: 5 µg/kg days 5 to 12
  - GM-CSF will not be used.
- The use of erythropoietin for the treatment of anaemia will not be permitted

#### **4.7 CRITERIA FOR STOPPING TREATMENT**

Protocol treatment may be stopped in the following instances:

- Evidence of progressive disease according to RECIST criteria on CT scan (appendix 4)
- Unacceptable toxicity
- An early toxicity assessment (after 20 patients have completed treatment in each arm) for safety reasons will be carried out. Data will be reviewed by the TMG.
- Intercurrent illness which, in the clinician's opinion, would require discontinuation of protocol therapy.
- If subsequent histological/cytological review is contrary to the original diagnosis
- Patient's request

For patients with measurable disease, evidence of minor disease progression (stable disease by RECIST criteria) is not a requirement to stop treatment in an otherwise clinically and symptomatically stable patient.

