### 4.1 CHEMOTHERAPY

Patients should start chemotherapy within two weeks of randomisation and within two weeks of a clinical assessment of fitness (section 4.1.1). Chemotherapy is cisplatin and etoposide and is given for 4 to 6 cycles. One cycle is given prior to radiotherapy. The second cycle in both arms is given concurrently with radiotherapy if possible. Radiotherapy will start on day 22 of cycle 1. In the BD radiotherapy arm, the third to sixth cycles (if applicable) are given after completion of the thoracic radiotherapy. In OD radiotherapy arm, the third & fourth cycles of PE are also given concurrently and the fifth & sixth cycles (if applicable) are given after completion of the thoracic radiotherapy.

Centres will be given the choice to stop chemotherapy after 4 cycles or to continue to up to 6 cycles. Centres who decide to give 6 cycles will have to continue doing so for all patients entered in the trial (unless it is decided that it is not in the patients best interest to receive cycle 5 and 6 or due to patient's choice)

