#### 4.1.2 Chemotherapy Administration

The chemotherapy doses should be based on the patient's calculated pre-treatment body surface area using actual body weight. A detailed plan for administering a cycle of chemotherapy including suggested hydration and anti emetics is given in appendix 6.

**In summary**, centres can opt for one of the two chemotherapy regimen. Cycles are given at 3 weeks intervals:

- Etoposide  $100 \text{ mg/m}^2$  iv D1-3  
Cisplatin  $75 \text{ mg/m}^2$  iv D1
- Or**
- Etoposide  $100 \text{ mg/m}^2$  iv D1-3  
Cisplatin  $25 \text{ mg/m}^2$  iv D1-3

Patients should be encouraged to take a high oral fluid intake on the day prior to cisplatin chemotherapy.

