**Etoposide and Cisplatin every 21 days for 4-6 cycles****Etoposide**

100 mg/m^2 days 1-3 BSA daily administered as an intravenous infusion over 1 hour every 3 weeks

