Toxicity will be assessed according to NCI Common Terminology Criteria for Adverse Events V.3.0. The proportion of patients experiencing a grade of 3 or above acute toxicity, including acute and/or late radiation morbidity, will be compared between the treatment groups using  $\chi^2$  and Fisher Exact tests. Acute toxicity will be defined as toxicities occurring from commencement to 3 months after completion of treatment; late toxicity will be defined as toxicities occurring between 3 months and 2 years after completion of treatment. All patients treated with at least one dose of cisplatin and etoposide will be evaluated for tumour response and included in the analysis of tumour response rates.

Response will be assessed according to Response Evaluation Criteria In Solid Tumours (RECIST) criteria. The proportion of patients in each treatment group whose best response (up to approximately 28 days post cycle 4 or, if stopped prior to cycle 4, approximately 28 days after last chemotherapy cycle given) from randomisation is complete or partial will be compared using  $\chi^2$  and Fisher Exact tests.

Safety analyses will be performed for all randomised patients treated with at least one dose of chemotherapy. Adverse effects will be summarised and compared between the two arms. The relative chemotherapy and RT dose intensity (RDI) will be summarised by calculating the median, SD, IQR and range for patients in each randomised treatment group. The RDI will be compared between the treatment groups by using the Wilcoxon Rank Sum test.

A detailed description of patient disposition will include a summary of the following:

- ▶ All patients entered and enrolled: overall, by treatment arm and by country
- ▶ Reasons for patients entered but not enrolled
- ▶ All enrolled patients treated with study drug, by treatment arm
- ▶ Reasons patients enrolled but not treated with study drug
- ▶ Reasons patients discontinued study drug treatment
- ▶ All important protocol violations.

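### The early toxicity review in section 4.7 sets no minimum follow-up after radiotherapy, and on schedule it observes each 66 Gy patient for 26 days less after radiotherapy than a 45 Gy patient

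*Supplement*

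**What the plan says.** The protocol's section 4.7, on criteria for stopping treatment, contains the only safety review tied to a patient count: "An early toxicity assessment (after 20 patients have completed treatment in each arm) for safety reasons will be carried out". It adds: "Data will be reviewed by the TMG". It does not say whether completion means the end of chemoradiotherapy, of all chemotherapy or of prophylactic cranial irradiation (PCI). It gives no data cut-off, no minimum follow-up and no list of toxicities to tabulate. The SAP does not mention this review.

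The schedules are explicit. For both arms, section 4.1 says: "Radiotherapy will start on day 22 of cycle 1". The control schedule in section 4.3.1 is "45 Gy in 30 twice daily fractions over a period of 19 days (radiotherapy to start on a Monday), 5 consecutive days a week"; the experimental schedule in section 4.4.1 is "66 Gy in 33 daily fractions over a period of 45 days (radiotherapy to start on a Monday), 5 consecutive days a week". On chemotherapy, section 4.1.2 says "Cycles are given at 3 weeks intervals", and appendix 6 gives etoposide on "days 1-3 BSA daily administered as an intravenous infusion over 1 hour every 3 weeks". Centres choose 4 or 6 cycles (section 4.1).

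The SAP, in line with protocol section 7.3.1, sets the reporting window: "Acute toxicity will be defined as toxicities occurring from commencement to 3 months after completion of treatment". Section 5.1 makes grade 3 and 4 radiation oesophagitis and pneumonitis serious adverse events whatever their other consequences.

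**The concern.** The plan's own acute window extends 3 months beyond treatment, so it expects relevant events after the last dose. The trigger for the early review requires none of that time. The two arms also reach completion at different distances from the end of radiotherapy, because the BD course finishes well before the last chemotherapy cycle and the OD course runs up to cycle 4. If the TMG compares counts of radiation toxicity at that moment, the experimental arm has had less time to show events that arise after radiotherapy.

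What is at stake is the weight of an early safety look at 66 Gy. A table that looks reassuring could partly reflect shorter observation of the arm that most needs watching.

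**Working it through.** **1. Reproduce the stated durations.** From a Monday start, 5 days a week:

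- BD: 30 fractions at 2 a day = 15 treatment days = 3 working weeks; 2 × 7 + 5 = 19 days. This matches section 4.3.1.
- OD: 33 fractions = 6 full weeks + 3 days; 6 × 7 + 3 = 45 days. This matches section 4.4.1.

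**2. End dates on schedule** (day 1 = first chemotherapy day).

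- Last radiotherapy day = 22 + duration − 1: BD 22 + 19 − 1 = day 40; OD 22 + 45 − 1 = day 66.
- Last chemotherapy day for c cycles = 1 + 21(c − 1) + 2: day 66 for 4 cycles, day 108 for 6.
- Completion is the later of the two: day 66 or day 108, the same in both arms.

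**3. Observation after radiotherapy on the day of completion.**

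- 4 cycles: OD 66 − 66 = 0 days; BD 66 − 40 = 26 days.
- 6 cycles: OD 108 − 66 = 42 days; BD 108 − 40 = 68 days.
- 4 cycles, with PCI counted at its latest date (section 4.5, 6 weeks): 42 against 68 days.
- 4 cycles, waiting for the toxicity form due 30 days after the last cycle (section 6.5): 30 against 56 days.

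The difference is 26 days each time.

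**4. Follow-up of the whole group of 20 at the trigger.** The documents give no data cut or accrual pattern, so this step is an assumption: even accrual, equal arms, no delays, and a cut on the day the 20th patient completes. Planned accrual is 532 / 48 = 11.08 a month, or 5.54 per arm, so one patient per arm every 30.44 / 5.54 = 5.49 days. Patient i has b + 5.49 × (20 − i) days after radiotherapy, with b from step 3. The mean is b + 5.49 × 9.5 = b + 52.2, and the maximum is b + 5.49 × 19 = b + 104.4.

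| Accrual per month | Cycles | Mean days, OD | Mean days, BD | Under 90 days, OD | Under 90 days, BD |
|---|---|---|---|---|---|
| 11.08 (planned) | 4 | 52 | 78 | 17 of 20 | 12 of 20 |
| 11.08 (planned) | 6 | 94 | 120 | 9 of 20 | 5 of 20 |
| 5.54 (half) | 4 | 104 | 130 | 9 of 20 | 6 of 20 |
| 2.77 (quarter) | 4 | 209 | 235 | 5 of 20 | 3 of 20 |

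On the first row the OD range is 0 to 104 days, and 14 of 20 OD patients have at least 30 days. Capping each OD patient at 91 days gives a mean of about 51, so 51 / 91 = 56% of the acute window has been observed.

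**5. Place in the trial calendar.** At planned accrual, 40 patients are entered by 40 / 11.08 = 3.6 months and finish 4 cycles by about month 6. The first IDMC report is due at about month 12 (section 7.2.1), and 6 × 11.08 ≈ 66 more patients are randomised in between. At half the rate the review falls at about 7.2 + 2.2 = 9.4 months, and 2.6 × 5.54 ≈ 14 are randomised in between.

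**The case against.** A reader might infer that the 66 Gy arm has no follow-up after radiotherapy at this review, or that the review cannot show toxicity following the experimental schedule. The documents support neither. Zero days is a floor. It applies only to a 4-cycle patient on the day of completion, in effect the 20th; the others have been followed for longer, and everything that happens during the 45-day OD course is visible. Several features lift the floor: 6-cycle centres, the policy of delaying chemotherapy to keep full dose (section 4.1.3) while radiotherapy does not wait (section 4.2), PCI if it counts as treatment, and a wait for the 30-day toxicity form. Centres must also pass radiotherapy QA before they randomise, which makes a slow start likely and lengthens follow-up in both arms. All of this stands. None of it sets a minimum.

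It is also fair to say that section 4.7 promises an assessment and not a formal comparison, and that both arms are observed to the same day when time runs from the start of treatment. The shortfall exists on the clock that starts at the end of radiotherapy. That clock matters only for events arising after radiotherapy, so a claim that every between-arm contrast favours OD would go too far.

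Other safeguards exist. Grade 3 and 4 radiation oesophagitis and pneumonitis are reported within 24 hours, with no time limit stated for these two items. Patients are seen weekly until acute effects resolve (section 6.2), and the IDMC reviews the data at least annually (section 9.0). These reduce the risk, but individual reports are not a comparison over equal time, and the IDMC dates are set by the calendar. Finally, the documents give no onset times for pneumonitis, so the size of any under-count cannot be calculated.

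**Conclusion.** The point holds in a limited form. The early review requires no follow-up after radiotherapy, and on schedule the experimental arm is 26 days behind the control arm on that clock for either number of cycles. With planned even accrual and 4 cycles, mean follow-up is about 52 days (OD) against 78 (BD), and 17 of 20 OD patients have not finished the 3-month acute window. The review is therefore likely to under-count toxicity arising after radiotherapy, more so at 66 Gy. The 26 days rests only on the stated schedules. The means and counts rest on the accrual and data-cut assumptions in the working, and follow-up roughly doubles if accrual halves.

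A reader might go on to infer that most of the acute window is unobserved, or that patients are unprotected until the IDMC meets. Neither follows: about 56% of OD patient-time in the window is observed under the same assumptions, and expedited reporting runs throughout. The primary analysis is unaffected. This is a worthwhile, inexpensive improvement to a stated safety check.

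**What to change.** - Keep the look already planned in section 4.7, and state what counts as completed treatment and where the data are cut.
- Repeat the same tabulation on the same 20 patients per arm once each has reached 3 months after completing treatment, the end of the protocol's acute window.
- In both looks, tabulate grade 3 and 4 radiation oesophagitis and pneumonitis by time since the end of thoracic radiotherapy, over equal time in both arms, with the number still under observation. Waiting alone is not enough: on 4 cycles it would leave about 91 days (OD) against 91 + 26 = 117 days (BD).

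The cost is one extra tabulation for the TMG about 3 months later, or about a month more if it waits for the first follow-up form as timed in section 6.5. It uses forms and visits already scheduled. No patients, visits or recruitment pause are added, and no dose or treatment rule changes.

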#### **4.8 THERAPY AFTER PROTOCOL TREATMENT HAS STOPPED**

Treatment after relapse or on withdrawal of patient from protocol treatment is at the discretion of the participating clinician, as deemed appropriate according to the clinical situation. Palliative radiotherapy to areas outside the original radiotherapy treatment volume and second-line chemotherapy can be used according to local practice.

#### **4.9 PATIENTS NOT MEETING THE RADIOTHERAPY PLANNING REQUIREMENTS**

If the V20 lung, dose to the spinal cord and heart do not meet the protocol requirements, the treatment decision will be left to the local investigator, as some adjustments may be necessary regarding the radiotherapy treatments. We strongly recommend that the total dose of radiotherapy is dropped to meet the normal tissue constraints.

These patients, who would have been randomised prior to the first cycle of chemotherapy, will be included in the intention to treat analysis. A subanalysis will be done excluding patients with protocol violations.

## 5.0 PHARMACOVIGILANCE

---

### 5.1 DEFINITIONS

**Adverse Event (AE):** any untoward medical occurrence in a patient or clinical trial subject administered a medicinal product and which does not necessarily have a causal relationship with this treatment. *An AE can therefore be any unfavourable and unintended sign (including an abnormal laboratory finding), symptom, or disease temporally associated with the use of an investigational medicinal product (IMP), whether or not considered related to the IMP.*

**Adverse Reaction (AR):** all untoward and unintended responses to an IMP related to any dose administered. *All AE's judged by either the reporting investigator or the sponsor as having reasonable causal relationship to a medicinal product qualify as adverse reactions. The expression reasonable causal relationship means to convey in general that there is evidence or argument to suggest a causal relationship.*

**Unexpected Adverse Reaction:** an AR, the nature and severity of which is not consistent with the applicable product information (i.e. summary of product characteristics (SmPC) for cisplatin and etoposide which are authorised products). *When the outcome of the adverse reaction is not consistent with the applicable product information this adverse reaction should be considered as unexpected. Side effects documented in the SmPC, which occur in a more severe form than anticipated, are also considered to be unexpected.*

**Serious Adverse Event (SAE):** for this trial an Adverse Event will be considered serious and require expedited reporting if it:

- results in **death** (within 30 days of last dose of chemotherapy or radiotherapy, irrespective of causality)
- is **life-threatening\*** (and is considered related to study treatment)
- requires **hospitalisation\*\***, or prolongation of existing hospitalisation (and is considered related to study treatment).
- results in persistent or significant **disability or incapacity**, (and is considered related to study treatment)
- is a **congenital anomaly or birth defect**

In addition the following will also be considered serious adverse events:

- **grade 3 and 4 radiation oesophagitis**
- **grade 3 and 4 radiation pneumonitis**

**SERIOUS ADVERSE EVENTS REQUIRE REPORTING TO THE CHIEF INVESTIGATOR WITHIN 24 HOURS, SEE SECTION 5.3 FOR FURTHER INFORMATION ON REPORTING PROCEDURES.**

Please note the following additional guidance with relation to definition of serious adverse events:

- Serious events not meeting the criteria outlined above: Medical judgement should be exercised in deciding whether an AE/AR is serious in other situations. Important AE/AR's that are not immediately

life-threatening or do not result in death or hospitalisation but may jeopardise the subject or may require intervention to prevent one of the other outcomes listed in the definition above, should also be considered serious.

- \*Life-threatening events: The term 'life-threatening' in the definition of 'serious' refers to an event in which the patient was at risk of death at the time of the event; it does not refer to an event which hypothetically might have caused death if it were more severe.
- \*\*Events requiring or prolonging hospitalisation: Hospitalisation is defined as an inpatient admission, regardless of length of stay, even if the hospitalisation is a precautionary measure for continued observation. Hospitalisations for a pre-existing condition, including elective procedures that have not worsened, do not constitute an SAE. Hospitalisations for palliative care, chemotherapy or radiotherapy, procedures or diagnostic procedures do not need to be reported.
- Progressive disease or death due to progressive SCLC does not need reporting as an SAE.

